**Audio recording:** All participants must agree to audio recording of treatment and assessment sessions for fidelity, training, and supervision purposes. As this is mandatory, it is part of the regular consent process. The audio recordings will not be shared with anybody outside of the research team or used for any other purpose so no additional audio recording consent will be obtained. Recordings will be transferred to and kept on CHEAR's secure pediatric servers for up to 3 years after the study is completed or whenever fidelity rating is completed, whichever comes first.

**Data Collection and Management:** The data for this study will include a number of different methods of collecting data, including interviews, surveys and tasks. The survey will be available as a secure web-based survey. All surveys will be identified with the unique study ID rather than any identifying information. Following the first assessment visit, participants will be given the option of completing some surveys via the secure-web-based survey format prior to attending the in-person visit to reduce the amount of time they need to be present at CHEAR. If participants do not complete the surveys in advance, they will complete them as part of the visit. All surveys provided to be completed at home will include information that does not warrant immediate follow-up (i.e., no questions about suicidal ideation or self-harm). All surveys will be identified with the unique study ID rather than any identifying information. The psychophysiological data will need to be post-processed and entered and will be duplicate entered to minimize error. The data manager will evaluate range and means of all data collected and will identify data entry errors weekly. The data manager will create scales and will verify range and means. The data manager, along with [name], will merge the data in preparation for analyses. These protocols have been successful in our other studies.

The data collected in this study once de-identified will be retained for future studies by UCSF or VA collaborators. These future studies will only have access to de-identified data. The only identifying information would include dates that participants attended treatment and assessments.

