*The Eating Disorder Examination-Questionnaire (EDE-Q) (baseline, mid-treatment, post-treatment, 6-month follow-up and monthly throughout treatment)* will be used to evaluate the frequency of binge eating episodes without the participant burden associated with the interview and shape and weight concerns. The EDE-Q has adequate psychometric properties. Only the three binge eating questions will be administered monthly. Participants respond to the following questions about binge eating; a) Over the past 28 days, how many times have you eaten what other people would regard as an unusually large amount of food? b) On how many of these times, did you have a sense of having lost control over your eating? c) Over the past 28 days, how many days have such overeating episodes occurred (i.e. you have eaten an unusually large amount of food and have a sense of loss of control at the time)? From these questions, number of binge eating episodes (eaten a large amount of food and felt a sense of loss of control) over the past 28 days and number of days participant experienced a binge eating episode can be calculated. We will also administer a modified question to identify monthly episodes of loss of control without large amount of food. a) Over the past 28 days, how many times did you have a sense of having lost control over your eating without having eaten an unusually large amount of food?

*Anthropometry (baseline, mid-treatment, post-treatment, 6-month follow-up and all treatment visits):* Height will be measured using a portable Schorr height board (Schorr Inc, Olney, MD) in triplicate. Height will be recorded to the nearest 0.1 cm for all trials, and the average of the 3 values will be used for analysis. Body weight in kilograms will be measured in duplicate on a Tanita Digital Scale (model WB-110A). Body weight will be recorded to the nearest 0.1 kg and the average of the 2 values will be used for analysis. Height and weight will be converted to body mass index ( $BMI=[kg/m^2]$ ). Waist circumference will be measured using a tape measure around the participant's middle around the waist and the measure recorded to the nearest cm will be recorded. The measurement will be taken 2-3 times and the average value maintained for analysis.

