**The Godin Leisure-Time Exercise Questionnaire** (GLTEQ; baseline, mid-treatment, post-treatment, 6-month follow-up and monthly during treatment) assesses the frequency and occurrence of leisure time physical activity. Participants report the number of times during a typical week that they engage in mild, moderate and strenuous exercise for more than 15 minutes.

**Feasibility (throughout treatment).** Feasibility will be assessed by Veteran attendance at treatment sessions.

**Acceptability (post-treatment only).** Acceptability will be assessed by survey, created by the study team based on established surveys used for [name] previous NIH-funded studies (R01DK075861; R01DK094475). Likert-type ratings will be used to respond to questions, such as "How much did you enjoy the treatment?" and "How helpful did you find the treatment?"

**Adherence (throughout treatment, post-treatment and 6-month follow-up).** We will capture the amount of self-monitoring and the extent to which it is complete for all participants during treatment. Following treatment, we will ask participants to report to what extent they are following treatment recommendations.

**Additional Food responsiveness tasks** to food and non-food cues will be measured by the *stop signal task-food version*. On each trial, participants are asked to discriminate between a picture of calorically-dense food or neutral object (e.g, chair). The two primary outcomes, stop signal reaction time for food pictures (SSRT-food) and neutral pictures (SSRT-neutral) will be compared to assess for food-specific impulsivity versus general impulsivity. Also, the

**Dot-Probe** (attention bias to food) task will be used. During this task two stimuli (unhealthy food and other stimuli (either neutral object/healthy food)) are presented simultaneously side by side followed by a probe appearing in the location of one of the stimuli. Participants are instructed to respond as quickly as possible by pressing a corresponding key on a button box to indicate the location of the probe (similar to the dot probe task). Each trial starts with a central fixation cross, which remains on the screen for 100 ms. Subsequently, the target stimuli pair is presented for 200 ms or 2000 ms randomly. The probe is presented until the participant responds.

| Measure                       | Instrument                           | Baseline | During TX | Mid TX | Post TX | 6-mo F/U |

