*Quality control, fidelity and supervision of assessments.* All assessors will be advanced graduate students, postdoctoral fellows or clinical psychologists who will attend a 2-day training with [name] (study personnel) on the assessment methods for this study. All assessors will be videotaped and scored for adherence to the assessment procedures and certified by [name] prior to working with study participants and will attend assessment supervision meetings with [name] weekly. Assessment sessions will be audiotaped for ongoing performance monitoring. Random samples (e.g. 30% or more) of all interview sessions will be rated for fidelity by an independent rater using a measure created for this study and will be blind to treatment condition.

**Maximizing Retention.** A systematic protocol will be followed to minimize subject attrition. Participants who miss a visit will be called by the group leader for counseling by telephone unless the missed visit was reported in advance (e.g., vacation). For each data collection visit, participants will be scheduled by telephone, sent written reminders, and called the day before the visit. Email addresses and phone numbers of the participants will be collected. Missed data collection visits will be rescheduled and followed up at least 3 times. If necessary, transportation to the clinic will be provided. If a participant withdraws from the study and does not wish to complete the full follow-up assessments, he or she will be given the option of having only his or her weight and binge eating assessed or self-reported in return for a \$25 gift card at each assessment time point (mid-treatment, post-treatment, and follow-up) that remains after the point at which he or she withdrew.]

In order to ensure high retention of our sample, we will request personal e-mail addresses and cell phone numbers as well as contact information for two close friends or relatives to further enhance our ability to locate participants. In addition, after the first data collection is complete, we plan to send birthday, winter and summer holiday cards and newsletters in order to maintain updated addresses that will permit future contacts. Even if the participant moves multiple times before the follow-up survey administration, interim address information will be helpful in confirming location of an individual.

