## **Analyses Plan**

**Primary Aim 1:** Feasibility will be evaluated through the assessment of attendance and retention rates of individuals in the ROC and CBT treatments for treatment completers, dropouts and number of sessions attended. Logistic regression models will be used with planned covariates and baseline BMI to estimate between-group difference in odds of treatment completion, defined by receiving a sufficient dose of treatment (i.e. >70% of sessions). Cox proportional hazards models adjusted with planned covariates and baseline BMI to evaluate differences between groups in time to dropout defined as missing four consecutive treatment sessions. Descriptive data will be calculated and between-group differences in counts of sessions attended will be compared between groups using a generalized linear model to accommodate expected non-normal distributions and will include planned covariates and baseline BMI in the model. Model selection will proceed by testing assumptions and improvements in fit afforded by candidate models that could account for over-dispersion or a large number of participants with no-missed sessions (e.g. Poisson vs. negative binomial or zero-inflated counts). To assess acceptability, we will use linear models adjusted with planned covariates and baseline BMI to estimate between-group differences on the acceptability questionnaire, a continuous measure of both satisfaction and liking of the treatment they received.

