#### **20. COMPENSATION FOR PARTICIPATION**

All participants will receive incentives at the following levels for time and effort: baseline = \$50, mid -treatment = \$50, post-treatment = \$100, 6-month follow-up = \$150. Participants who withdraw, but who wish to have their weight and binge eating measured or self-report their weight and binge eating to study staff at follow-up time points will receive a \$25 gift card at each assessment time point (mid-treatment, post-treatment, mid-follow-up, and follow-up) that remains after the point at which he or she withdrew. Participants who enroll and complete all assessment visits can earn up to \$350.

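### Acceptability, part of Primary Aim 1, is surveyed only at post-treatment, and no rating is planned from participants who withdraw and decline full follow-up, so the arm comparison can be biased and each arm's mean is likely overstated

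*Protocol*

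**What the plan says.** Section 6 (Specific Aims) puts feasibility and acceptability together in Primary Aim 1. In Section 9, Measures, the acceptability survey is headed "Acceptability (post-treatment only", and Table 2 agrees, with a single mark under post-treatment.

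The Maximizing Retention paragraph covers a participant who withdraws and does not want the full follow-up: "he or she will be given the option of having only his or her weight and binge eating assessed or self-reported", for a $25 gift card at each remaining time point. Section 20 repeats the offer for those who "wish to have their weight and binge eating measured or self-report their weight and binge eating to study staff at follow-up time points". Neither place includes acceptability.

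The same retention paragraph keeps pursuing people who miss visits without withdrawing: "Missed data collection visits will be rescheduled and followed up at least 3 times". The Analyses Plan treats leaving treatment as a separate event, with "time to dropout defined as missing four consecutive treatment sessions".

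For Primary Aim 1 the Analyses Plan states: "To assess acceptability, we will use linear models adjusted with planned covariates and baseline BMI to estimate between-group differences on the acceptability questionnaire". It mentions no other acceptability rating.

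**The concern.** A satisfaction survey given once, at the end, to those still willing to attend is answered by a group selected partly by the quantity being measured. People who disliked a treatment enough to withdraw are those whose ratings matter most, and the protocol plans none from them.

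The protocol gives reasons to expect such leaving, possibly unequally by arm:
- The stopping-rules paragraph considers drop-outs or poor recruitment likelier than adverse events to halt the trial.
- The Analyses Plan models between-arm differences in time to dropout.
- Only ROC includes in-session food exposures, which Section 14 says may provoke negative emotions, and only ROC prescribes physical activity.
- Section 15 allows staff to withdraw a participant whom treatment is affecting badly.

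Binge eating and BMI are measured repeatedly, so a likelihood-based model can draw on a participant's earlier values. Acceptability has no earlier value to draw on. An analysis plan could impute from baseline covariates and attendance, but it cannot recover ratings that were never collected.

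At stake are the arm comparison on a primary-aim outcome and the absolute level of acceptability reported for each treatment.

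**Working it through.** **The plan's own figures.** There are none to reproduce. The protocol gives no dropout rate, acceptability SD, alpha, power or allocation ratio.

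**Inputs**
- From the protocol: at least 120 randomised to two arms, and one acceptability rating, at post-treatment.
- Assumed: 60 per arm, two-sided 0.05, a normal approximation, and the leaving shares and rating gaps below.

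Here, leaving means withdrawing and giving no post-treatment rating.

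**Overstatement of an arm's mean.** Let p be the share leaving and g the gap in SD by which leavers would rate below stayers. The mean over all randomised is the stayers' mean minus p × g, so a respondents-only mean is too high by p × g. With p = 0.20 and g = 0.5 to 1.0, that is 0.10 to 0.20 SD. It occurs even when the arms lose equal numbers.

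**Bias in the arm difference.** Bias = p_ROC × g_ROC − p_CBT × g_CBT. With the same gap in both arms this is g × (p_ROC − p_CBT). The false-positive columns apply when there is no true difference over all randomised.

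| Leaving, ROC / CBT | Bias, g = 0.5 | False-positive rate | Bias, g = 1.0 | False-positive rate |
|---|---|---|---|---|
| 20% / 20% | 0 | 5.0% | 0 | 5.0% |
| 25% / 20% | 0.025 SD | 5.2% | 0.05 SD | 5.7% |
| 30% / 20% | 0.05 SD | 5.6% | 0.10 SD | 7.6% |
| 40% / 20% | 0.10 SD | 7.4% | 0.20 SD | 14.8% |
| 35% / 15% | 0.10 SD | 7.6% | 0.20 SD | 15.6% |

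Worked example, last row with g = 1.0:
- Respondents: 60 × 0.65 = 39 and 60 × 0.85 = 51.
- Standard error: √(1/39 + 1/51) = 0.213 SD.
- Bias over standard error: 0.20 / 0.213 = 0.94.
- Rejection rate: 1 − Φ(1.96 − 0.94) + Φ(−1.96 − 0.94) = 0.156.

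The bias favours the arm that loses more people.

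**Equal leaving, unequal gaps.** With 20% leaving both arms and gaps of 1.0 and 0.3 SD, bias = 0.20 × (1.0 − 0.3) = 0.14 SD. Unequal leaving is not required.

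**Scale.** With 60 per arm, the difference detectable at 80% power is (1.96 + 0.84) × √(2/60) ≈ 0.51 SD.

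**Self-reported weight, only if such values were analysed with measured ones.** Bias = under-reporting in kg × difference between arms in the share self-reporting. With an assumed 1 to 3 kg and 5 to 20 points, this runs from 1 × 0.05 = 0.05 kg to 3 × 0.20 = 0.6 kg. At an assumed height of 1.70 m, dividing by 1.70² gives 0.02 to 0.21 BMI units.

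**The case against.** **Who is missed.** Stopping treatment is not the same as withdrawing. Someone who misses four sessions in a row but stays enrolled is still due the full post-treatment visit, is contacted repeatedly, can be given transport and is paid. A reader might infer that everyone who leaves treatment is never asked about acceptability. The documents do not support that: the planned gap covers those who withdraw and also decline full follow-up. This narrows the group and may make it small, but it does not fill the gap.

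**Size.** At a 5 to 10 point difference in leaving, the bias is 0.025 to 0.10 SD, well below the roughly 0.51 SD the trial could detect. That stands as a limit on the arm comparison. It does not cover the overstated arm means.

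**Early ratings.** In ROC, visits 1 to 8 deal with hunger and satiety and visits 9 to 16 with craving exposures, so an early rating judges a different part of treatment. That also stands. It argues against treating an early rating as a final one, not against collecting it.

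**The wider reading.** A reader might also infer that withdrawers' self-reported weight and binge eating are pooled with scale weights and interview counts, biasing Primary Aims 1 to 3. The protocol does not say this:
- The phrase about using all available data is in the Primary Aim 2 paragraph, where it explains likelihood estimation with missing cases. It is not a rule on measurement source, and the Primary Aim 3 paragraph does not contain it. Which values enter which model is ordinarily settled in an analysis plan.
- The completion, time-to-dropout and session-count analyses rest on attendance.
- The EDE-Q and BES are self-rated for everyone, so a change of mode concerns mainly the EDE interview, and no instrument is named for withdrawers.
- Energy intake is not in the reduced package, so it would be missing rather than self-reported.
- Barring self-reports from the primary models would exchange reporting error for informative missingness.

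**Conclusion.** The point holds for acceptability. A primary-aim outcome is collected once, and the reduced contact offered to withdrawers leaves it out. The respondents-only comparison can therefore be biased, and each arm's mean is likely overstated.

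Under the assumptions above, the bias in the arm difference is 0.025 to 0.20 SD, with a false-positive rate of about 5% to 16%. It is zero if the share leaving and the rating gap are the same in both arms. These figures rest on assumed leaving shares and gaps, 60 per arm and two-sided 0.05; the real size is unknown. The direction for the arm means assumes that leavers would rate lower than stayers.

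On self-reported weight and binge eating, the supportable conclusion is narrower. The protocol allows these values but does not provide for recording how each was obtained, and that information is hard to reconstruct later. It does not follow that the values are pooled or should be excluded. The attendance-based part of Primary Aim 1 is unaffected.

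**What to change.** 1. Add the enjoyment and helpfulness items to the reduced contact for withdrawers, and to the brief monthly survey already given during treatment.
2. Analyse acceptability in all randomised participants with any rating, using a repeated-measures model with each rating placed at the time it was given. Do not carry a last rating forward. Keep the post-treatment-only linear model as a sensitivity analysis.
3. Report by arm how many participants gave no rating at all.
4. Record at collection whether each weight and binge-eating value was measured, taken by interview or self-reported, so that a measured-only sensitivity analysis is possible. Do this for all participants: the list of modifications adds virtual assessments in April 2020 and does not say how weight was then obtained. "Body weight in kilograms will be measured in duplicate on a Tanita Digital Scale (model WB-110A" describes the in-person standard.

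The cost is a few survey items and one source field; both contacts already exist, and the withdrawal contact is already paid. The drawbacks are a slightly longer survey, early ROC ratings that reflect only the part of treatment received, and continued absence of ratings from anyone who leaves before the first monthly survey and refuses all contact.

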## **Analyses Plan**

**Primary Aim 1:** Feasibility will be evaluated through the assessment of attendance and retention rates of individuals in the ROC and CBT treatments for treatment completers, dropouts and number of sessions attended. Logistic regression models will be used with planned covariates and baseline BMI to estimate between-group difference in odds of treatment completion, defined by receiving a sufficient dose of treatment (i.e. >70% of sessions). Cox proportional hazards models adjusted with planned covariates and baseline BMI to evaluate differences between groups in time to dropout defined as missing four consecutive treatment sessions. Descriptive data will be calculated and between-group differences in counts of sessions attended will be compared between groups using a generalized linear model to accommodate expected non-normal distributions and will include planned covariates and baseline BMI in the model. Model selection will proceed by testing assumptions and improvements in fit afforded by candidate models that could account for over-dispersion or a large number of participants with no-missed sessions (e.g. Poisson vs. negative binomial or zero-inflated counts). To assess acceptability, we will use linear models adjusted with planned covariates and baseline BMI to estimate between-group differences on the acceptability questionnaire, a continuous measure of both satisfaction and liking of the treatment they received.

**Primary Aim 2:** Efficacy of ROC and CBT on changes in binge eating (*as measured by the EDE; EDE-Q and BES*), at mid-treatment, post-treatment and 6-months post-treatment timepoints. LME models with dummy-coded indicators for planned treatment comparisons between ROC and CBT, and a continuous term for time selected after evaluating non-linearity. Between-group (ROC vs. CBT) differences in change in binge eating (Primary Aim 2) will be estimated in models with planned covariates (age, gender), baseline BMI, and corresponding baseline values for each outcome. The GLME for counts of binge episodes and LME model for continuous symptom inventories provide maximum likelihood parameter estimates based on all of the available data, allowing for the inclusion of cases with missing data and the modeling of the covariance error structure of the data across the assessment points. Interactions of between-group indicator and time will assess whether differences in binge eating dissipate from active treatment compared to the 6-month follow-up timepoint.

**Primary Aim 3:** Efficacy of ROC and CBT on changes in weight loss (BMI) and energy intake (kcal/day), at mid-treatment, post-treatment and 6-months post-treatment time points will be evaluated with (G)LME models. Between-group (ROC vs. CBT) differences in change in BMI and energy intake will be estimated in models with planned covariates (age, gender), and corresponding baseline values for each outcome.

**Secondary Aim 1:** Efficacy of ROC and CBT on changes in food responsivity (FR scale; psychophysiological responding to food, reward-based eating) and satiety responsiveness (SR scale, WLT), using GLME adjusted for corresponding baseline values and planned covariates mirroring primary analyses. We also will use (G)LME to assess between-group differences in measures of reactivity to food cues using psychophysiological measures of EMG (salivation), heart rate and HRV at each follow-up.

**Exploratory Aim 1:** This aim will evaluate whether 1) individual factors including baseline age, gender, binge eating status, satiety responsiveness, responsivity to food cues, or reward-based eating moderate the impact of ROC vs CBT on improvements in binge eating and weight by evaluating two interaction terms in primary outcome models, and whether 2) improvements in responsivity to food cues, satiety responsiveness, reward-based eating or physical activity mediate improvements in binge eating and weight, by screening each in single mediator models prior to estimating joint effects food cue responsiveness, satiety responsiveness, or reward-based eating mediate improvements in binge eating, using a multiple mediator model. Significance tests of indirect effects will be assessed using a product of coefficients method with bootstrap estimation of 95% confidence intervals.

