**Research Design.** This study will randomize at least 120 overweight and obese male and female Veterans with BED or subclinical BED to one of two arms (ROC or CBT). The study data manager, who will have no contact with research participants, will conduct randomizations and monitor allocations throughout the study to alert the PI of any systematic differences in additional demographics (age, race/ethnicity) that may arise.

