## Treatment Arms

Both interventions arms will be matched on contact frequency and time. All treatment groups will include up to 20 participants, will be 60 minutes in length and will meet weekly for 4 months, and twice monthly for the 5th month

Table 1. Differences between ROC and CBT

|                                       | ROC                                                                                                                                                                                                                                                                          | CBT                                                                                   |
|---------------------------------------|------------------------------------------------------------------------------------------------------------------------------------------------------------------------------------------------------------------------------------------------------------------------------|---------------------------------------------------------------------------------------|
| Dietary prescription           | Sessions focus on learning to control physiological and psychological responding to food, and to eat less of foods that are palatable when physically sated. Participants will learn general food intake literacy, to pick nutritious foods, and physiological energy needs. | None
Participants are encouraged to incorporate a variety of foods into their diet |
| Self-monitoring                | Hunger, craving and food intake                                                                                                                                                                                                                                              | Antecedents, behaviors, consequences and thoughts surrounding binge episodes          |
| Experiential learning          | Participants bring meals and/or palatable foods to each session. Hunger and satiety is monitored in session during meals. Exposures to highly craved foods are conducted in session.                                                                                         | None                                                                                  |

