| Physical activity prescription | Physical activity is used to help regulate physiological and psychological responding to food cues.                                                                                                                                                                          | None                                                                                  |
| Goal setting                   | Goal setting focuses on self-monitoring and practicing mastery and toleration of physiological /psychological arousal, as well as food intake and physical activity                                                                                                          | Goal setting focuses on self-monitoring of food intake, thoughts and behaviors.       |
| Coping skills                  | Methods for managing psychological and physiological arousal. Discussed each week in regards to mastery and toleration of physiological /psychological arousal.                                                                                                              | Cognitive restructuring, stress management, behavior chains to reduce binge eating    |

(total treatment duration = 5 months, 18 meetings). Descriptions of the treatment arms follow and key differences between the treatment arms are outlined in Table 1. All treatment sessions will be audiorecorded for supervision and fidelity purposes.

**Regulation of Cues (ROC).** The ROC program provides psychoeducation, coping skills, self-monitoring and experiential learning. Physical activity will be promoted to improve self-regulatory strength and to help participants master and tolerate physiological and psychological arousal, resist cravings and overeating.

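### Primary Aim 1 models sessions attended, capped at 18, with unbounded count models whose zero inflation acts at the wrong end of the scale; on assumed attendance this costs about 20 points of power

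*Protocol*

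**What the plan says.** The Treatment Arms section fixes the length of the programme: groups "meet weekly for 4 months, and twice monthly for the 5th month", summarised as "total treatment duration = 5 months, 18 meetings".

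Under Primary Aim 1, the Analyses Plan reports attendance and retention "for treatment completers, dropouts and number of sessions attended". Three analyses follow:

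- **Completion**, by logistic regression, "defined by receiving a sufficient dose of treatment (i.e. >70% of sessions").
- **Dropout**, by Cox regression, with "time to dropout defined as missing four consecutive treatment sessions".
- **Attendance**: "between-group differences in counts of sessions attended will be compared between groups using a generalized linear model". The model is to be chosen by testing assumptions and comparing fit among candidates that allow for over-dispersion or "a large number of participants with no-missed sessions (e.g. Poisson vs. negative binomial or zero-inflated counts").

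On size, the Research Design paragraph states: "This study will randomize at least 120 overweight and obese male and female Veterans".

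**The concern.** The attendance outcome and its candidate models do not match in two ways.

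1. The outcome is bounded at 18, and high attendance is the hoped-for result, so the data should pile up near that bound. None of the three named families has an upper bound.
2. Someone with no missed sessions has attended 18. Zero inflation adds probability at zero attended, the opposite end. The feature the text wants to handle is one that the named remedy cannot reach when sessions attended is the outcome.

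Feasibility is a primary aim, and this is its main between-arm comparison of attendance. A badly scaled variance distorts the standard error for that comparison.

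A smaller matter is that the completion and dropout rules are set side by side, with nothing said about a participant who meets both or who leaves too late to meet the dropout rule.

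**Working it through.** **Number of sessions.** Four months of four weekly sessions plus two: 4 × 4 + 2 = 18. This reproduces the protocol's figure.

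**How far the named models stray past the bound.** For a Poisson count, the probability above 18 is 3.7% at mean 12, 11.7% at mean 14, 18.1% at mean 15 and 25.8% at mean 16. A model for sessions out of 18 puts nothing there.

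**Assumed attendance (not in the documents).** There are 60 per arm, taking the 120 as equally split. A fraction p leaves after k sessions, with k uniform on 0 to 8 and every session before leaving attended. The rest attend each session with probability 0.92. No covariates are used.

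- Stayers: mean 18 × 0.92 = 16.56; variance 18 × 0.92 × 0.08 = 1.32.
- Leavers: mean 4; variance 80/12 = 6.67.
- Arm mean = (1−p) × 16.56 + p × 4.
- Arm variance = (1−p) × 1.32 + p × 6.67 + p(1−p) × 12.56².

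| p | mean | variance | share at 18 = (1−p) × 0.92¹⁸ | share at 0 = p/9 |
|---|---|---|---|---|
| 0.15 | 14.68 | 22.2 | 19% | 1.7% |
| 0.25 | 13.42 | 32.2 | 17% | 2.8% |
| 0.35 | 12.16 | 39.1 | 14% | 3.9% |

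The spike is at 18, not at zero.

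**Type I error.**

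- Plain Poisson understates the variance by φ = variance/mean. For p = 0.15, φ = 22.2/14.68 = 1.52 and the true level is 2 × [1 − Φ(1.96/√1.52)] = 11%. For p = 0.25, φ = 2.40 and the level is 21%. Simulation gives 9-23%.
- Choosing between Poisson and negative binomial by AIC selects the negative binomial in 88-100% of simulated trials. Type I error after selection is about 0.5-2%. Runs of the negative binomial alone gave 1-5%.
- A logit model for the share of 18 with robust standard errors gives 5-7%.

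**Power, 15% against 35% early leavers.** With correct standard errors:

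- difference = 14.68 − 12.16 = 2.51
- SE = √((22.2 + 39.1)/60) = 1.01
- z = 2.51/1.01 = 2.49
- power = Φ(2.49 − 1.96) = 70%

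| Analysis | Simulated power |
|---|---|
| Chosen by fit (negative binomial on attended) | about 49% |
| Logit model, share of 18, robust SEs | about 70% |
| Poisson on attended, robust SEs | about 68% |
| Negative binomial on sessions missed | about 70% |

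With about 600 trials, Monte Carlo error on a power near 50% is 1.96 × √(0.25/600) = 4 points. A gap of about 20 points is well outside it.

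**Completion and dropout rules.** Completion needs more than 0.70 × 18 = 12.6, so at least 13 attended and at most 5 missed.

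- Stopping after session 13 (72.2%) or 14 (77.8%) meets both rules.
- Patterns meeting both: one run of exactly 4 misses, 15; a run of 5, 14; a run of 4 plus one separate miss, 2 × 13 + 13 × 12 = 182. Total 15 + 14 + 182 = 211 of 2¹⁸ patterns. These are not equally likely, so this shows only that overlap is possible.
- Leaving after session 15, 16 or 17 leaves 3, 2 or 1 sessions, too few for four misses. With full earlier attendance, such people have at least 15/18 = 83% and count as completers.
- Expected numbers, assuming a leaving hazard of 1-3% per session and intermittent misses of 5-20%: about 1-3 of 120 meet both rules, and about 3-6 of 120 leave without being flagged. If leaving happens only after 0-8 sessions, overlap is about 0.02-0.05 of 120.

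**The case against.** **The model list is illustrative and will be tested for fit.** The list is introduced as examples, and the plan promises to test assumptions. A reader who sees the Poisson type I error might infer that the plan will produce false positives. The documents do not support that: the text anticipates over-dispersion, and a fit comparison would discard plain Poisson. This part of the objection stands. However, every model named is unbounded, so the search ends on one that is conservative and loses power.

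**The text may mean sessions missed.** That is plausible, since zero inflation then acts at the right end and the upper bound hardly matters (at a mean of 3 missed, the Poisson probability above 18 is about 6 × 10⁻¹⁰). But the stated outcome is sessions attended, so this reading also needs a correction.

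**The gain does not come from the bounded family.** This is largely true. Robust standard errors on a Poisson model recover nearly all of it, so the figures do not show that only a logit model will do.

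**Completion and dropout measure different things.** This stands. A reader might infer that the two rules contradict each other. They do not: one is dose received and the other is a run of absence, they are analysed in separate models, and nothing says they must be exclusive. Nor does the plan ignore the 18-session programme altogether, because the completion rule is a proportion of it.

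**Timing dropout at the last session attended would be worse.** A reader might see this as the natural repair. It would turn an isolated miss at session 18 into a dropout event. With 8% random misses among the 90-102 of 120 who continue, that is 0.08 × 90 = 7.2 to 0.08 × 102 = 8.2 false events, more than the 3-6 late leavers it would recover.

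**Conclusion.** The attendance comparison is wrongly specified as written. A count with a ceiling of 18 is given unbounded models, and the zero-inflation option addresses the end where few participants are expected. That mismatch follows from the protocol's own text and needs no assumption.

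Its size does rest on assumptions. Under the attendance pattern above, the planned search yields a test with type I error of about 0.5-2%, and power of about 49% where about 70% is available. Other attendance patterns would change these figures. The error is conservative: the likely harm is a missed difference in attendance, not a spurious one.

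The dropout point is minor. The overlap with completion and the blind window over the last three sessions are real, but the numbers affected are small and the two outcomes can properly coexist. It calls for a clarifying sentence, not a new definition.

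**What to change.** 1. Analyse sessions attended out of 18 with a logit-link binomial model and robust standard errors. Alternatively, change the outcome to sessions missed, so that zero is the no-missed end, again with robust standard errors. Name the chosen model in place of the search over unbounded models for sessions attended.
2. State that completion and dropout are separate outcomes that may overlap in the same participant, and that the Cox analysis cannot detect leaving in the last three sessions.

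Both are changes of wording. Attendance is already recorded throughout treatment, so no new data or visits are needed. The cost is in interpretation: the effect becomes an odds ratio for attending a session, or a ratio of missed sessions, instead of a ratio of sessions attended. Reporting mean sessions attended per arm alongside keeps the result readable.
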